# Protocol for a feasibility randomized controlled trial to evaluate the efficacy, safety and tolerability of N-acetylcysteine in reducing adverse drug reactions among adults treated for multidrug-resistant tuberculosis in Tanzania

**DOI:** 10.1186/s40814-023-01281-7

**Published:** 2023-04-01

**Keywords:** Multidrug-resistant tuberculosis, Adverse drug reactions, N-acetylcyteine, Drug-induced Liver injury, Clinical trial

## Abstract

**Background:**

Adverse drug reactions (ADRs) frequently occur in patients using second-line anti-tuberculosis medicine for treatment of multidrug resistant tuberculosis (MDR-TB). ADRs contribute to treatment interruptions which can compromise treatment response and risk acquired drug resistance to critical newer drugs such as bedaquiline, while severe ADRs carry considerable morbidity and mortality. N-acetylcysteine (NAC) has shown promise in reducing ADRs for medications related to TB in case series or randomized controlled trials in other medical conditions, yet evidence is lacking in MDR-TB patients. TB endemic settings have limited capacity to conduct clinical trials. We designed a proof-of-concept clinical trial primarily to explore the preliminary evidence on the protective effect of NAC among people treated for MDR-TB with second-line anti-TB medications.

**Methods:**

This is a proof-of-concept randomized open label clinical trial with 3 treatment arms including a control arm, an interventional arm of NAC 900 mg daily, and an interventional arm of NAC 900 mg twice-daily administered during the intensive phase of MDR-TB treatment. Patients initiating MDR-TB treatment will be enrolled at Kibong’oto National Center of Excellence for MDR-TB in the Kilimanjaro region of Tanzania. The minimum anticipated sample size is 66; with 22 participants in each arm. ADR monitoring will be performed at baseline and daily follow-up over 24 weeks including blood and urine specimen collection for hepatic and renal function and electrolyte abnormalities, and electrocardiogram. Sputum will be collected at baseline and monthly thereafter and cultured for mycobacteria as well as assayed for other molecular targets of *Mycobacterium tuberculosis*. Adverse drug events will be analysed over time using mixed effect models. Mean differences between arms in change of the ADRs from baseline (with 95% confidence intervals) will be derived from the fitted model.

**Discussion:**

Given that NAC promotes synthesis of glutathione, an intracellular antioxidant that combats the impact of oxidative stress, it may protect against medication induced oxidative damage in organs such as liver, pancreas, kidney, and cells of the immune system. This randomized controlled trial will determine if NAC leads to fewer ADRs, and if this protection is dose dependent. Fewer ADRs among patients treated with MDR-TB may significantly improve treatment outcomes for multidrug regimens that necessitate prolonged treatment durations. Conduct of this trial will set the needed infrastructure for clinical trials.

**Trial registration:**

PACTR202007736854169 Registered 03 July 2020

**Supplementary Information:**

The online version contains supplementary material available at 10.1186/s40814-023-01281-7.

## Key questions on feasibility

Tanzania is one of the sub-Saharan African countries facing a high burden of tuberculosis (TB) including the multidrug resistant (MDR)-TB and other infectious diseases, however the capacity to conduct research, particularly clinical trials, has been limited. We proposed to conduct a clinical trial among MDR-TB patients with the mains components of toxicity reduction and capacity development in clinical trials in Tanzania.To our knowledge, this is the first registered global trial to examine the protective effect of N-acetylcysteine (NAC) on occurrence of adverse drug reaction in MDR-TB patients treated with current recommended regimens that prioritize all-oral medications.

What uncertainties existed regarding feasibility?It was uncertain whether Tanzanian institutes would execute both sponsor/investigator responsibilities and trial management roles to address clinical research questions especially in one of the priority infectious diseases, MDR-TB.It was also uncertain whether a clinical trial unit established with managers, physicians, trialists and laboratory scientists would be set to execute all relevant clinical trials processes and confront infectious diseases using MDR-TB as a model disease.

What are the expected implications of the feasibility findings for the main study?This clinical trial aimed to minimize occurrence of adverse drug reactions in MDR-TB patients that would have a direct patient benefit but with additional components of the trial capacity for laboratory scientists, research trialists in order to create a rapid response infrastructure for other infectious diseases of public health priority. Furthermore, the trial will explore the preliminary evidence on the effect of NAC on the results that will guide design of the pragmatic clinical trial in Tanzania.

## Introduction

### Background and rationale

The crisis of multidrug-resistant tuberculosis (MDR-TB), defined as point mutations of *Mycobacterium tuberculosis* (MTB) chromosomes resulting in strains that are resistance to isoniazid and rifampicin, key medicines for the treatment of TB, continues to worsen [1]. In 2019, the World Health Organization (WHO) estimated 484,000 cases of MDR-TB, while approximately 156,000 were enrolled to initiate treatment. This marked a 21% increase in enrolment compared to the 2016 report [2]. With the growing epidemic of MDR-TB, further exacerbated by the COVID-19 pandemic [3], and a greater proportion of people accessing treatment, there is further urgency to assure treatment regimens are tolerable and completed without interruption which poses risk to individual outcomes and *M. tuberculosis* strains with amplified drug resistance [4]. Despite the priority for tolerable regimens, medicines used to treat MDR-TB are referred to as “second-line” because of reduced potency and a worse side effect profile [5]. Regimens are constructed of 4–6 drugs based on the susceptibility profile of the infecting *M. tuberculosis* strain, drug-drug interactions or individual contraindications, and supply chain availability [6]. New and repurposed drugs have improved the efficacy and shortened the duration of MDR-TB treatment but those medications have significant and often overlapping toxicities [7]. Based on data from controlled trials and large operational studies, the WHO has recently prioritized bedaquiline, linezolid, newer generation fluoroquinolones (moxifloxacin or levofloxacin), and clofazimine for the treatment of MDR-TB as well as consideration of other new agents such as delamanid and conventional anti-TB drugs such as cycloserine, pyrazinamide, ethionamide/prothionamide, and ethambutol to complete a multi-drug regimen [8]. While medications requiring intravenous or intramuscular injection are no longer preferred, there are some uncommon clinical scenarios where TB treatment programs or patients themselves may opt to include an injectable aminoglycoside (amikacin or streptomycin) or a carbapenem with beta-lactamase inhibitor (meropenem/clavulanate or imipenem-cilastin/clavulanate).

No other infectious disease requires treatment strategies of such quantity of drugs, and drug class diversity as MDR-TB, and combined toxicities are not dissimilar to treatment of hematological malignancy. As described elsewhere, the severe adverse drug reactions (ADRs) from medications used to treat MDR-TB include hepatotoxicity, cytopenias, QTc prolongation and cardiac arrhythmia, nephrotoxicity, ototoxicity, peripheral and optic neuropathy, and psychosis [9, 10]. Given the combination of drug-classes, including broad spectrum classes such as the fluoroquinolones, gastrointestinal side effects are common, and can even confuse the presentation of more serious ADRs including hepatoxicity and lactic acidosis [11]. For example, despite the efficacy of bedaquiline, up to 20.8% of people experience bedaquiline related ADRs, with 7.4% serious. ADRs related to bedaquiline were most frequently gastrointestinal (14%), followed by metabolic disorders (8.5%) and nervous system disorders (8.5%) [12]. Likewise, the inclusion of linezolid in MDR-TB regimen has a significant positive effect in improving treatment outcome and reducing mortality, yet the occurrence of ADRs include myelosuppression (33%), neuropathy (30%) whereas other less common ADRs are vomiting, hyperpigmentation and transient visual impairment [13]. Clofazimine is considered safe since the ADRs requiring discontinuation or withdrawal reported have been as low as 0.1% common ADRs are skin discolouration and gastrointestinal side effects with a pooled proportion of 22% [14]. Furthermore, several drugs have overlapping ADRs for instance the fluoroquinolones, bedaquiline, and delamanid all may cause QTc interval prolongation and hepatotoxicity [15].

We have designed the following trial to study a promising compound, N-acetylcysteine (NAC), for reduction of ADRs during the course of MDR-TB treatment, which is to our knowledge the first of its kind with this primary objective for MDR-TB. NAC is a thiol compound and the acetylated form of L-cysteine with the chemical formula C5H9NO3S and molecular weight of 163.2 g/mol. NAC is efficiently absorbed and metabolized primarily by the liver. Absorption provides a large amount of NAC for cellular uptake, deacetylation of cysteine, and synthesis of glutathione (GSH). GSH is an intracellular antioxidant that combats the impact of oxidative stress thus protecting the vital cellular components against the dangerous effect of peroxidation. The free sulfyhydryl group in GSH readily scavenges harmful radicals such as reactive oxygen species, peroxides and superoxides to thiyl radical, which rapidly dimerises to form glutathione disulfide [16, 17]. GHS released from NAC then carriers out its putative protective effect both enzymatically and non-enzymatically. The benefit of NAC on oxidative damage extend to organs such liver, pancreas, kidney, inner ear hair cells, and cells of the immune system. Furthermore, NAC demonstrates anti-inflammatory properties by limiting pro-inflammatory cytokine release, particularly through a NF-kappa beta pathway [18].

NAC has been employed in clinical practice for several decades. It has been used as a mucolytic agent and for the treatment of numerous disorders including paracetamol intoxication, doxorubicin cardiotoxicity, ischemia–reperfusion cardiac injury, acute respiratory distress syndrome, bronchitis, chemotherapy-induced toxicity, heavy metal toxicity and psychiatric disorders [19]. Most relevant to prevention of ADRs from MDR-TB treatment, previous NAC interventions have been trialed in drug susceptible (DS)-TB among primarily Asian populations [20, 21]. Baniasadi et al. conducted a clinical trial in an older age (≥ 60 years) population at higher risk of drug induced liver injury (DILI). The hepatoprotective effect of NAC was significant since anti-TB DILI occurred in 12 patients (37.5%) in the control group but none in the NAC group [20]. Farazi et al. conducted another NAC trial in 85 patients with age ≥ 50 years and treated for DS-TB [21]. Eligible participants were randomly selected to receive NAC 600 mg or placebo with standard rifampicin, isoniazid, pyrazinamide and ethambutol (RHZE) treatment. DILI occurred in 14.3% of the placebo group as signified by raised serum aspartate transaminases (AST), alanine transaminases (ALT) and bilirubin. Interestingly, the group receiving NAC also had reduced levels of AST, ALT and bilirubin compared to their baseline values [21]. A further meta-analysis by Kranzer et al. conducted a review on the efficacy and safety of NAC in preventing aminoglycoside induced ototoxicity and found the weight of evidence supporting the safety and otoprotective effect of NAC when co-administered with an aminoglycoside, even for durations shorter than those used for MDR-TB [22]. Thus, the prior studies in non-MDR-TB populations and among people with drug-susceptible TB provide a strong justification for a clinical trial to investigate the effect of concomitant NAC treatment in patients receiving MDR-TB treatment. If NAC allows uninterrupted use of the most efficacious dose and duration while limiting the long-term sequela of MDR-TB treatment, then the trial may indeed contribute to the current ambitious goals set by the global health community for achieving a 90% TB treatment success rate by 2035 [23]. Hence, conducting this randomized controlled trial within a MDR-TB program from a TB endemic country will provide actionable programmatic data with which to determine the eventual role of a NAC intervention.

## Clinical trial objectives

### Hypothesis I

Administration of oral NAC at a dose of 900 mg daily in combination with second-line during treatment of multidrug-resistant tuberculosis (MDR-TB) will protect against occurrence of serious advent events without interfering with the effect of second line anti-TB regimen.

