### Hypothesis II

Administration of oral NAC at a dose of 900 mg twice a day in combination with second-line during treatment of multidrug resistant tuberculosis (MDR-TB) will protect more than the dose of 900 mg daily against occurrence of serious adverse events without interfering with the effect of second line anti-TB regimen.

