## Primary objective

To explore the preliminary evidence on the protective effect of NAC through assessing the development of clinical or laboratory-based adverse drug reactions (ADRs) at any frequency during the first six months of local standard of care MDR-TB treatment among patients receiving NAC at a dose of 900 mg daily or 900 mg twice a day compared to those patients treated with the standard of care regimen and placebo.

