## Trial design

NAC trial is a phase 2b randomized open labelled superiority trial with three parallel groups and a primary endpoint of occurrence of ADRs at any time during treatment for MDR-TB.

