## Outcomes

### Primary endpoint

The primary outcomes of interests include feasibility metrics related to implementation of sponsor/investigator responsibilities and trial management roles, knowledgeable and skilled trial manager, physician trialists, and laboratory scientists. Evidence generated through this process will guide on the design of the pragmatic trial of NAC in MDR-TB patients.

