## Statistical methods

### Statistical methods for primary and secondary outcomes

The primary efficacy analysis will be conducted using laboratory measurement. Analysis that will be performed includes both Modified Intent to Treat (MITT) defined as analysis of all randomised participants and a Per Protocol (PP) defined as comparison of three arms; control with either 900 mg OD or 900BD or both intervention arms in participants who completed the treatment originally allocated.

The difference in the proportion of patients with ADRs (as defined by the primary efficacy endpoint) between each treatment arm and control arm will be calculated with 95% confidence interval using standard methods**.** In addition, hearing threshold level will be analysed over time using mixed effect models to account for the longitudinal nature of the data. Mean differences between arms in change from baseline (with 95% confidence intervals) will be derived from the fitted model.

The incidence of severe adverse drug reactions as defined by Common Terminology Criteria for Adverse Event (CTCAE) will be calculated in percentage of affected individuals in each arm during the exposure time period of 6 months and the relative risks will be estimated. Time to stable conversion in both phenotypic and molecular (TB molecular bacterial load assay) MTB monitoring methods will be calculated and compared in each arm using adjusted and unadjusted hazard ratio with log-rank test. Furthermore, the rate of patients in each arm converting to negative sputum culture at 4 or 6 or 8 months after treatment initiation will be estimated. Kaplan-Meir estimator will be used to estimate the proportion of patients converting to negative culture and MBLA by specific time.

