### Adverse event reporting and harms

Adverse events will be collected by the investigator from the time a subject sign the Informed Consent Form through to their end of follow-up visit. Participants that will be early withdrawn, will only have SAEs collected at the time of withdrawal. Any AE (serious or non-serious) observed by the investigator or reported by the subject will be recorded on the Adverse Event Case Report Form. The investigator will review each AE and assess its severity and relationship to drug treatment based on all available information at the time of the completion of the case report form. AE with relationship with drug treatment will be termed as ADRs and severity grading will be according to the CTCAE.

In the case where an overall diagnosis cannot be made, each specific sign and/or symptom will be recorded as individual AEs. Documentation of the date of onset, and stop date (duration) if applicable will be done. The AEs will also be described in severity, and action taken with IMP while concurrently describing the action taken to the participant. The outcome and relationship to IMP will be recited. Also, the occurrence and seriousness of the AEs will be documented.

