## Abbreviations

ADR: Adverse drug reaction
AE: Adverse event
ALT: Alanine transaminase
AST: Aspartate transaminase
AUC: Area under the curve
CTCAE: Common Terminologies Criteria for Adverse Events
CTMG: Clinical Trial Monitoring Group
DILI: Drug-induced liver injury
DSMB: Data Safety Monitoring Board
EDCTP: European and Developing Countries Clinical Trials Partnerships
GCP: Good Clinical Practice
GSH: Glutathione
ICF: Informed Consent Form
ICH: International Conference of Harmonization
ICIDR: International Consortium for Infectious Diseases Research
KIDH: Kibong’oto Infectious Diseases Hospital
MDRTB: Multidrug-resistant tuberculosis
MITT: Modified intention to treat
MTB: *Mycobacterium tuberculosis*
NAC: N acetylcysteine
PACTR: Pan-African Clinical Trial Registry
PanACEA: Pan-African Consortium for Evaluating Anti-TB Antibiotics
PID: Patients identification
PK: Pharmacokinetics
PP: Per-protocol
REDCap: Research Electronic Data Capture
SADR: Severe adverse drug reaction
TB: Tuberculosis
WHO: World Health Organization

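### Hypotheses I and II are stated on serious adverse events, but no listed endpoint or named analysis separates events by seriousness

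*Protocol article*

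**What the plan says.** Under Clinical trial objectives, Hypothesis I states that NAC 900 mg daily "will protect against occurrence of serious advent events without interfering with the effect of second line anti-TB regimen". Hypothesis II states that 900 mg twice daily "will protect more than the dose of 900 mg daily against occurrence of serious adverse events".

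The other statements of the question use different outcomes:

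- The Primary objective speaks of "assessing the development of clinical or laboratory-based adverse drug reactions (ADRs) at any frequency during the first six months".
- Trial design names "a primary endpoint of occurrence of ADRs at any time during treatment for MDR-TB".
- The Primary endpoint section of Outcomes puts feasibility first: "The primary outcomes of interests include feasibility metrics related to implementation of sponsor/investigator responsibilities and trial management roles".
- The secondary endpoints are the proportion of AEs, the proportion attributed to the experimental treatment, regimen changes caused by ADRs, and time to an AE including SADRs. Abbreviations gives "SADR: Severe adverse drug reaction".
- Statistical methods compares the proportion with ADRs in each NAC arm against control, and adds: "The incidence of severe adverse drug reactions as defined by Common Terminology Criteria for Adverse Event (CTCAE) will be calculated". Relative risks follow.

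Adverse event reporting and harms grades severity by CTCAE and defines an ADR as an AE related to drug treatment. It then adds, as a further item: "Also, the occurrence and seriousness of the AEs will be documented".

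**The concern.** Severity is the intensity of an event. Seriousness is a separate classification, usually based on outcome or consequence. They pick out different patients. For example, a high-grade but symptomless rise in ALT is severe and need not be serious, while a moderate event that leads to hospital admission is serious and not severe. The hypotheses are also not confined to drug-related events, whereas an ADR is drug-related by the article's own definition.

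At stake is what the trial may say about its own hypotheses. A finding on any ADR, or on CTCAE-severe ADRs, does not bear directly on a hypothesis about serious events. The trial is meant to guide a later pragmatic trial, so the outcome on which protection is hypothesised should be stated the same way throughout.

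**Working it through.** No figure in the plan depends on this point. The sample size does not help to settle which outcome is meant: 3 x 20 = 60, and 60 x 1.10 = 66 reproduces the stated total, but the article says that no formal power calculation was done, so 66 is tied to no event rate. The check is therefore a comparison of sections.

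**Step 1. Which outcome does each section use?**

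| Section | Outcome | Drug-related only? | Separated by seriousness? |
|---|---|---|---|
| Hypotheses I and II | Serious adverse events | No | Yes |
| Primary objective | Any clinical or laboratory ADR | Yes | No |
| Trial design | Occurrence of ADRs | Yes | No |
| Outcomes, primary endpoint | Feasibility metrics | Not applicable | No |
| Outcomes, safety and tolerability | All AEs; AEs attributed to experimental treatment | First no, second yes | No |
| Outcomes, efficacy | Regimen changes due to ADRs; time to AE including severe ADRs | First yes; second covers AEs | No |
| Statistical methods | Proportion with ADRs; incidence and relative risk of CTCAE-severe ADRs | Yes | No |

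Only the two hypotheses use seriousness.

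**Step 2. Does the article itself treat the two words as one?** No. Adverse event reporting and harms assigns a CTCAE grade for severity and records seriousness as another item. It refers to AEs as serious or non-serious, and limits collection at early withdrawal to SAEs. Interventions makes serious events related to NAC a reason to stop trial medication. Seriousness is thus a category of its own in this document.

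**Step 3. Does any measured outcome stand in for the hypothesised one?**

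- CTCAE-severe ADRs: neither set contains the other, for the reasons given above.
- Any ADR: includes non-serious reactions and leaves out unrelated serious events.
- All AEs: contains every recorded serious event, but mixed with all the others. A difference between arms in all AEs does not show a difference in serious ones.

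**Step 4. Does the contrast fit Hypothesis II?** Write p0, p1 and p2 for the ADR proportions under control, once-daily and twice-daily NAC. Statistical methods names p1 - p0 and p2 - p0. Hypothesis II concerns p2 - p1. The point estimate follows, since (p2 - p0) - (p1 - p0) = p2 - p1. Its interval cannot be taken by treating the two planned differences as independent, because they share the control arm. With v0, v1 and v2 as the variances of the three proportions, the needed variance is v1 + v2, while the planned ones are v1 + v0 and v2 + v0. The dose contrast is easy to calculate from the arm-level data, but the ADR analysis does not name it.

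**The case against.** The strongest reply is that 'serious' is a slip for 'severe'. Hypothesis I is loosely edited, the introduction moves between the two words, and the abstract and discussion present severe ADRs as the motivation. Read as 'severe', Hypothesis I would map well onto the CTCAE analysis. That is plausible, but the article does not say so, the word stands in both hypotheses, and a slip would still need correcting.

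A second reply is that an SAE table by arm is routine and may be left to the full protocol or the analysis plan. This stands in part: the absence of such a table from an article would not be a finding alone. What remains is that the hypotheses, endpoints and analyses are all printed here and name different outcomes.

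Three stronger readings are tempting and are not supported:

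- A reader might infer that the hypotheses cannot be answered at all. Seriousness is documented for AEs, so a comparison could be derived from the recorded data.
- A reader might infer that a rise in serious events under NAC would go unseen. Serious events are counted, undivided, in the all-AE endpoints, and the DSMB reviews unblinded data about every six months.
- A reader might take the 7.4% serious figure in the introduction as this trial's event rate and calculate expected counts or power. That figure concerns bedaquiline alone, its denominator is unclear, and the trial's regimens contain several drugs. No such estimate is made here.

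**Conclusion.** The conflict is real and lies in the printed text. Both efficacy hypotheses are stated on serious adverse events, and none of the listed endpoints or named analyses isolates those events. As written, the named analyses do not test the hypotheses. Hypothesis II has a second gap, since the ADR comparison names only each NAC arm against control.

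The size is modest. The point concerns outcome wording, one missing descriptive endpoint and one unnamed contrast. It affects neither data collection nor sample size, and no numerical effect is claimed. The part of the hypotheses about not interfering with the anti-TB regimen is not in question, since culture and pharmacokinetic endpoints address it.

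The conclusion assumes that 'serious' and 'severe' carry the separate meanings that the adverse event section gives them. If the sponsor meant 'severe', the correction to the outcome is a change of word, and the dose contrast still needs to be named.

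**What to change.** 1. Restate Hypotheses I and II on the outcome that the trial analyses: ADRs over the first six months, with CTCAE-severe ADRs, as the protocol defines them, as the severe category.
2. Use 'serious' and 'severe' as distinct terms throughout.
3. List the number and proportion of participants with at least one SAE, by arm, as a secondary endpoint, reported descriptively.
4. For Hypothesis II, report the twice-daily minus once-daily difference in the ADR proportion with its 95% confidence interval, beside the two comparisons with control.

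The cost is a wording change and one or two extra table rows from data already recorded. The downside is that the hypotheses become more modest. The SAE row should be read as description and not as evidence of protection, since the trial was not sized for any outcome.
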